Laser acupuncture (LA) is a non-invasive modality that applies low-dose laser stimulation to acupoints, combining principles of traditional acupuncture with modern photobiomodulation (18, 19). It is particularly suitable for needle-sensitive populations (e.g., children, the elderly) and has shown promise in improving sleep and mood symptoms by regulating neuroendocrine function and reducing inflammation (20, 21). Photobiomodulation is thought to exert its effects by stimulating mitochondrial cytochrome c oxidase, thereby enhancing cellular energy metabolism and modulating redox signaling (22–24). These changes may regulate neuroendocrine and immune pathways, contributing to the normalization of 5-HT and CORT levels relevant to sleep–wake regulation (25–27). Nevertheless, robust clinical trials investigating LA for depression-related insomnia are scarce, and its effects on underlying biological mechanisms remain poorly elucidated.

Despite its potential, significant evidence gaps exist regarding LA’s efficacy, mechanisms, and applicability in treating insomnia in MDD patients (28, 29). Few high-quality trials have specifically evaluated LA for this comorbidity, and none have comprehensively assessed its impact on sleep quality alongside biomarker changes (29, 30). Furthermore, the mechanisms by which LA may influence objective sleep outcomes and biochemical markers (e.g., 5-HT, CORT) are not yet established (31, 32). This study aims to address these gaps by evaluating the clinical efficacy and safety of LA in improving sleep quality—assessed via the Pittsburgh Sleep Quality Index (PSQI)—and depressive symptoms in MDD patients, and by exploring its potential effects on serum 5-HT and CORT levels. We hypothesize that LA will be superior to sham laser acupuncture (SLA) and standard care in improving sleep quality, reducing depressive symptoms, and modulating biomarker levels, offering a well-tolerated and non-invasive therapeutic option.

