### Randomization, allocation concealment and blinding

Stratified permuted block randomization will be applied to assign participants to the LA, SLA, and control groups in a 1:1:1 ratio. Stratification will be based on age (18–40 vs. 41–60 years) and gender (male vs. female), resulting in four strata: (1) males aged 18–40 years, (2) males aged 41–60 years, (3) females aged 18–40 years, and (4) females aged 41–60 years. Within each stratum, randomization sequences will be generated using permuted blocks to ensure balance until a total of 40 participants per group are enrolled (120 in total).

The randomization sequence will be generated by an independent research assistant who is not involved in the study, using GraphPad QuickCalcs, a validated web-based program for generating block randomization schemes. Allocation codes will be sealed in sequentially numbered opaque envelopes prepared by independent personnel. At enrolment, envelopes will be opened in sequence by study staff according to the order of patient visits, ensuring allocation concealment. Participants will be informed that they have an equal probability of assignment to each of the three groups.

This study will be conducted as a single-blind trial. Participants, outcome assessors, data collectors, and statisticians will remain blinded to group allocation, while acupuncturists delivering the interventions cannot be blinded due to the nature of the procedures. To maintain blinding integrity, acupuncturists will strictly follow a standardized intervention manual to minimize performance bias.

During treatment, participants will receive therapy in a closed room and will be required to wear blindfolds to prevent observation of laser irradiation. Communication among participants will be restricted, and scheduling will minimize cross-interaction. Researchers will not access unblinded data until data collection and statistical analysis are complete. Allocation concealment and restricted data access will further reduce the risk of bias, thereby strengthening the methodological rigor of the trial.

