SLA procedures. The sham condition used sham laser applied to the same acupoints as the LA group. Identical probes were secured with medical tape and positioned per the standardized manual, but the device delivered 0 mW output while maintaining the same indicators (lights/sounds) to preserve blinding. Session structure (per-point exposure time, total duration, number of sessions, and treatment sequence) matched the active protocol. Participants and outcome assessors were blinded; operators followed a standardized script. Regarding the validity of sham laser as a control procedure for laser acupuncture studies, in a study which evaluated the use of SLA as a control procedure by comparing verum laser with sham laser reported that treatment with verum laser was indistinguishable from sham laser and there was also no difference in the deqi-like sensations felt by study participants when comparing verum laser with sham laser. Then, the authors also analyzed the pooled findings of three RCTs that compared the use of sham laser with needle acupuncture and found that the credibility of sham laser was not different from that of needle acupuncture (39). Hence, sham laser can serve as valid placebo procedure in laser acupuncture studies.

Control group. Participants in the control arm will continue their stable antidepressant regimen without additional intervention. This group establishes a baseline comparator, enhancing the validity of between-group analyses.

Medication uses across groups. Antidepressant therapy must remain stable for ≥2 weeks before enrolment and throughout the trial. Rescue medication will be limited to oral eszopiclone 0.5 mg, to be taken as needed when insomnia persists for ≥3 consecutive nights. No other sedative–hypnotics (including benzodiazepines) will be permitted unless clinically necessary for safety; any exception requires documentation and approval by the principal investigator. All rescue-medication use will be logged (date, time, dose, indication) and reviewed regularly by the research team. If insomnia worsens alongside depressive symptoms, the participant will be withdrawn and referred for further management.

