### Sample size calculation

Sample size estimation was performed using G*Power version 3.1.9.2 (Heinrich Heine University, Düsseldorf, Germany) (49). The calculation was based on a repeated-measures, between–within interaction analysis of variance (ANOVA) with the changes in PSQI across time as the primary outcome. An effect size of f = 0.158 was adopted from a RCT investigating LA in patients with co morbid insomnia, depression and anxiety (50). This effect size was chosen as a conservative estimate, reflecting clinically meaningful but mild improvements in sleep quality. Parameters were set at a two-tailed significance level (α) of 0.05, statistical power (1–β) of 0.80, number of groups = 3 and number of measurements = 3. Under these conditions, the minimum required sample size was calculated to be 84 participants across three arms. To account for an anticipated dropout or attrition rate of approximately 30%, the final adjusted sample size was set at 108 participants, with 36 subjects per group (LA, SLA, and control). This sample size is expected to provide sufficient power to detect between-group differences and to remain robust against missing data or attrition.

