### Statistical methods

All analyses will be conducted using statistical package for the social sciences (SPSS) version 28.0 (IBM Corp., Armonk, NY, USA) (51). Continuous variables will be summarized as mean ± standard deviation (SD) for normally distributed data, or as median (interquartile range, IQR) for non-normally distributed data. Categorical variables will be expressed as frequencies and percentages. A two-tailed p value < 0.05 will be considered statistically significant.

Primary outcomes. Changes in PSQI scores, sleep efficiency, total sleep time, and number of awakenings will be analyzed using a mixed-design ANOVA (52), with intervention group (LA, SLA, control) as the between-subject factor and time (baseline, post-treatment, follow-up) as the within-subject factor. Standardized mean differences will be calculated as effect sizes. Significant interactions will be followed by *post-hoc* pairwise comparisons. All primary analyses will follow the intention-to-treat (ITT) principle, with participants analyzed according to initial randomization regardless of adherence or withdrawal.

Secondary outcomes. ISI, HAMD-17, and biomarker levels (CORT, 5-HT) will be analyzed as continuous variables using mixed ANOVA across three time points. Actigraphy-derived sleep parameters will be analyzed similarly. Dropout rates due to AEs will be compared among groups using Pearson’s χ² test or Fisher’s exact test, as appropriate.

A subgroup analysis will be performed in which participants treated with LA will be subdivided into those on selective serotonin reuptake inhibitor (SSRI), serotonin noradrenaline reuptake inhibitor (SNRI) and other antidepressants and on low to moderate dose (less than optimal dose of antidepressant) and on high dose (above the optimal dose of antidepressant) using generalized estimated equation (GEE) where the dependent variable is dummy coded as 0 = without sleep quality disturbance (PSQI ≤ 5) and 1 = with sleep quality disturbance (PSQI > 5).

Sensitivity analysis. A per-protocol analysis will be conducted using the same statistical tests, excluding participants who fail to complete at least 5 of the 6 weekly intervention sessions. Findings will be compared with ITT results.

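### The primary test and its 80% power belong to a three-arm omnibus interaction, while the hypothesis is pairwise; laser versus sham is only a gated post-hoc pair with no stated power

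*Protocol article*

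**What the plan says.** The Introduction states the hypothesis in pairs: "We hypothesize that LA will be superior to sham laser acupuncture (SLA) and standard care in improving sleep quality".

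Statistical methods (Primary outcomes) fixes a mixed-design ANOVA "with intervention group (LA, SLA, control) as the between-subject factor and time (baseline, post-treatment, follow-up) as the within-subject factor". Pairs come afterwards and conditionally: "Significant interactions will be followed by *post-hoc* pairwise comparisons". No pair and no time point is named as the primary contrast.

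Sample size calculation uses the same model: "The calculation was based on a repeated-measures, between–within interaction analysis of variance (ANOVA) with the changes in PSQI across time as the primary outcome". Its inputs are f = 0.158, α = 0.05, power 0.80, three groups and three measurements. The result is a minimum of 84, raised to 108 for about 30% attrition. The Abstract, Study design and Randomization sections give 120. The sample size section concludes: "This sample size is expected to provide sufficient power to detect between-group differences".

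On blinding, the Randomization section says: "Participants, outcome assessors, data collectors, and statisticians will remain blinded to group allocation". The control paragraph under Interventions says: "Participants in the control arm will continue their stable antidepressant regimen without additional intervention". The blinding assessment questions only the LA and SLA participants.

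**The concern.** A 4-df interaction asks whether the three arms change differently over time in any way at all. It can be significant because one arm departs from the other two, whichever arm that is. Here one arm is special for a reason unrelated to the laser. Control patients have been told there are three groups, and then receive no device. They must know they are not in a laser arm, and they report the primary outcome themselves. A response shared by LA and SLA, whether expectation or contact, would separate them from control. The limitations paragraph of the Discussion itself allows that sham contact at the same acupoints may have non-specific effects.

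A positive primary test would therefore be compatible with no laser effect. The comparison that isolates the laser, and in which participants can be blinded, is LA versus SLA. It is reached only through the interaction gate, and the sample size statement does not cover it.

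**Working it through.** **1. Reproduce the plan's figure.** The inputs f = 0.158, k = 3 groups, m = 3 times and α = 0.05 come from the sample size section. The article does not give the correlation between repeated measures or the sphericity correction; I assume ρ = 0.5 and ε = 1.

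- λ = f²·N·m·ε/(1 − ρ) = 0.024964 × 84 × 3/0.5 = 12.58
- df = (k − 1)(m − 1) = 4 and (N − k)(m − 1) = 162
- Power = 0.810 at N = 84, and 0.794 at N = 81, so 84 is the minimum in equal arms.

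Other settings do not return 84: ρ = 0.3, 0.4, 0.6 and 0.7 give 114, 99, 69 and 51; two groups give 66; two measurements give 102; ε = 0.75 gives 102. The 80% is thus power for the omnibus interaction. At N = 120 that power is 0.938.

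**2. Translate f into mean differences.** Take unit SD and an effect present at both t1 and t2. Then f = d × (SD of the arm pattern) × (SD of the time pattern), where d is the largest difference between arms. The time pattern (0, 1, 1) has SD √(2/9) = 0.471.

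- One arm differs from the other two: arm SD 0.471, so f = 2d/9 and d = 0.158 × 4.5 = 0.711.
- Graded (LA 1, SLA 0.5, control 0): arm SD √(1/6) = 0.408, so f = 0.1925d and d = 0.821. LA–SLA is half of that, 0.41.

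**3. Power for LA versus SLA at the same f.** The t0-to-t1 change has variance 2(1 − ρ) = 1. Power is from a noncentral t with noncentrality D/√(2/n) and 2n − 2 df, two-sided 0.05.

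| Pattern (all f = 0.158) | True LA–SLA | Omnibus, 28 / 40 per arm | LA vs SLA, 28 per arm | LA vs SLA, 40 per arm |
|---|---|---|---|---|
| LA = SLA, both better than control by 0.71 SD | 0 | 81% / 94% | 5% | 5% |
| Sham gives half the effect | 0.41 SD | 81% / 94% | 33% | 44% |
| SLA = control, LA better by 0.71 SD | 0.71 SD | 81% / 94% | 74% | 88% |

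In the last row, testing LA versus SLA as a 2 × 3 interaction gives 78% at 28 per arm and 91% at 40.

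Simulation with 20,000 runs agrees: in the first row the interaction is significant in 80.7% and 93.7% of trials, and LA versus SLA in about 5%.

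Baseline adjustment reduces the SD to √(1 − ρ²) = 0.866. At 28 per arm, power becomes 41% (half effect) and about 86% (SLA = control); at 40 per arm, 55% and 95%.

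**4. Cost of the gate.** Requiring the interaction and the t1 LA–SLA comparison both to be significant gives, by simulation at 28 per arm, 30% (half effect) and 68% (SLA = control), against 32% and 74% for the pair alone.

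**5. Detectable LA–SLA difference at 80% power**, from the same noncentral t:

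- 28 completers per arm (120 × 0.7 = 84): about 0.76 SD on change, or 0.76 × 0.866 ≈ 0.66 SD baseline-adjusted.
- 25 completers per arm (108 × 0.7 = 75.6): about 0.81 or 0.70 SD.

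**The case against.** Three replies have force.

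First, the plan does compare LA with SLA. It is one of the three pairs that follow a significant interaction. A reader might infer that the trial never tests the laser against sham; the text does not support that. What stands is that the comparison is conditional, is not the named primary contrast, and has no stated power.

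Second, a reader might infer that the pairwise tests carry no multiplicity correction, and quote an inflated error rate. The article neither specifies nor rules out a correction, and that detail may sit in the full protocol or analysis plan. No error-rate claim is made here on that basis.

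Third, a reader might infer that the trial is necessarily underpowered for LA versus SLA. It is not. If sham behaves like no treatment, power is 74–78% at 28 per arm and 88% at 40, and higher with baseline adjustment. The documents do not say which pattern underlies f = 0.158, what its comparator was, or what ρ is, so neither the favourable nor the unfavourable case can be assumed.

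It is also fair that the blinding check covers only LA and SLA, which suggests the authors regard participant blinding as a two-arm matter, and that actigraphy is less open to reporting bias. The Randomization section still says without exception that participants are blinded, and the declared primary outcome is the PSQI.

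**Conclusion.** The structural point holds firmly. The primary test does not match the pairwise hypothesis, and the 80% power is for the omnibus interaction only. The closing claim of sufficient power for between-group differences is therefore not shown for LA versus SLA. The statement that participants remain blinded cannot be true of the control arm.

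The size is conditional on ρ = 0.5, sphericity and an effect sustained at both later visits. With a response shared by LA and SLA, the primary test is significant in about 81% (28 per arm) to 94% (40 per arm) of trials with no laser effect. For the same f, and where a laser effect exists, LA-versus-SLA power at 28 per arm ranges from 33% to 74–78% in the two patterns examined. Because the documents fix neither pattern nor ρ, the finding is that this power is unstated and could be low, not that it is known to be low.

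**What to change.** 1. **Statistical methods.** Name LA minus SLA in PSQI at one prespecified time point (for example t1, end of treatment) as the primary contrast, two-sided 0.05, with no interaction gate. Test LA versus control next in fixed sequence. Keep the interaction and the other time point as secondary. Requiring both comparisons to succeed would also fit the hypothesis; the need is that the choice be fixed in advance.
2. **Randomization, allocation concealment and blinding.** State that control participants are not blinded, so that LA versus control is an open-label comparison on a self-reported outcome.
3. **Sample size calculation.** Say that the 80% refers to the omnibus interaction. After reconciling 108 with 120, give the detectable LA–SLA difference at 80% power: about 0.76 SD on change or 0.66 SD baseline-adjusted with 120 enrolled, or about 0.81 and 0.70 SD with 108, each after 30% loss and at ρ = 0.5.

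The changes themselves add no patients. The price is a less favourable power statement, an omnibus p-value that is no longer the headline, and an amendment to the primary-analysis text and the registry entry, to be made before any unblinded data are seen.

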## Abstract

**Background:**

Effective options for managing insomnia in major depressive disorder (MDD) remain limited. This randomized, single-blind, three-arm parallel trial will compare low-dose laser acupuncture (LA), sham laser acupuncture (SLA), and standard care, evaluating changes in sleep and mood alongside serum biomarkers at three time points (t0 = pre-treatment; t1 = post-treatment, 6 weeks; t2 = follow-up, 12 weeks after treatment).

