**Methods:**

A total of 120 inpatients meeting all eligibility criteria will be randomized (1:1:1) to LA, SLA, or control. The primary outcome is the Pittsburgh Sleep Quality Index (PSQI). Secondary outcomes include the Insomnia Severity Index (ISI), the 17-item Hamilton Depression Rating Scale (HAMD-17), serum 5-hydroxytryptamine (5-HT) and cortisol (CORT), and actigraphy. Outcomes are assessed at t0, t1, and t2. Safety will be evaluated by adverse events (AEs) and discontinuations due to adverse effects. Analyses will follow the intention-to-treat principle.

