## Outcomes

### Primary outcome

Quality of sleep. The primary outcome is global sleep quality assessed by the PSQI, a 19-item questionnaire widely used to evaluate sleep quality and disturbances over the past month (41). The PSQI includes 4 open-ended and several closed-ended items scored on a 4-point Likert scale, covering subjective sleep quality, sleep latency, sleep duration, sleep efficiency (SE), sleep disturbances, sleep medication use, and daytime dysfunction. The total score ranges from 0 to 21, with higher scores indicating poorer sleep quality and more severe disturbances. A cutoff point of more than 5 is considered as having significant disturbance in sleep quality, which demonstrates a sensitivity of 90% and specificity of 87% (41). The Chinese version of the PSQI has been validated among Chinese medical students, showing acceptable internal consistency (Cronbach’s α = 0.734) (42).

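### The primary PSQI analysis names neither the visit (t1 or t2) nor the pair of arms that decides, and the interaction test does not protect LA versus sham if both device arms beat control

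*Protocol article*

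**What the plan says.** The Primary outcome section defines the endpoint without a time: "The primary outcome is global sleep quality assessed by the PSQI". The abstract states that "Outcomes are assessed at t0, t1, and t2", and defines the two later visits as "t1 = post-treatment, 6 weeks; t2 = follow-up, 12 weeks after treatment". The Sample size calculation section sizes the trial on a between-within interaction, "with the changes in PSQI across time as the primary outcome".

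Under Statistical methods, the primary model has three groups and "time (baseline, post-treatment, follow-up) as the within-subject factor". The decision route is "Significant interactions will be followed by *post-hoc* pairwise comparisons". The only criterion given is general: "A two-tailed p value < 0.05 will be considered statistically significant".

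The Introduction states the hypothesis that LA is superior both to SLA and to standard care, again without a visit. The article does not rank the visits or the pairs, state an adjustment for the pairwise tests, or say how a difference at only one of t1 and t2 is to be read.

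**The concern.** The interaction test has no direction, no pair and no visit. A gap between control and the two device arms is enough to make it significant. It therefore cannot establish that LA is superior to SLA. That claim has to come from the pairwise comparisons, and there both the visit and the contrast are open.

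The two visits answer different questions. The PSQI covers the past month. At t1 that month lies inside the six-week treatment period; at t2 it begins about eight weeks after treatment ended. The first visit asks whether the treatment works, the second whether a benefit lasts. Results of t1 only, t2 only and both support different conclusions, and nothing in the article prevents each from being reported as success on the primary outcome.

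There is also an error-rate question. The control arm has no device, the PSQI is a questionnaire, and the Discussion concedes that sham applied at the same acupoints may have non-specific effects. A trial in which LA equals sham and both beat control is therefore a realistic case. In that case the interaction test is passed for a reason unrelated to the laser, and LA versus sham may then be tested at two visits.

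**Working it through.** **1. The plan's own figure.** Inputs from the Sample size calculation section: f = 0.158, α = 0.05, power 0.80, 3 groups, 3 measurements. The correlation between measurements is not given; 0.5 is assumed. With λ = f²·N·m/(1 − ρ):

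λ = 0.158² × 84 × 3 / 0.5 = 0.024964 × 504 = 12.58, with df 4 and 2 × (84 − 3) = 162.

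Power is 0.8105, so the stated 84 reproduces. It is the size for the omnibus interaction, not for LA versus SLA at a visit. It also depends on the assumed correlation: 0.3 gives 114 and 0.7 gives 51.

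**2. Two unadjusted tests without a gate.** If the tests at t1 and t2 were independent, the chance of at least one false difference is 1 − 0.95² = 0.0975. With correlation between the two tests it is 0.095 (0.3), 0.091 (0.5) and 0.084 (0.7).

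**3. With the interaction as gate.** Simulation, 20,000 trials per case: LA = SLA, control worse by a common shift at t1 and t2, interaction F test at 0.05, then unadjusted LA versus SLA t tests at t1 and t2. Assumptions: equal variances, compound symmetry, no dropout. The article leaves open whether the pairwise tests use visit scores or change from baseline, so both were run. Results for 40 per arm:

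| Control shift (SD) | Within-patient correlation | Gate passed | False LA vs SLA at t1 or t2, visit scores | Same, change scores |
|---|---|---|---|---|
| 0 | 0.3 | 0.052 | 0.016 | 0.025 |
| 0 | 0.7 | 0.051 | 0.009 | 0.025 |
| 0.5 | 0.3 | 0.487 | 0.065 | 0.072 |
| 0.5 | 0.7 | 0.884 | 0.079 | 0.089 |
| 0.8 | 0.3 | 0.913 | 0.094 | 0.088 |
| 0.8 | 0.7 | 0.999 | 0.086 | 0.091 |

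With 28 per arm (84 / 3) the same calculation gives about 8 to 9% at 0.8 to 1.0 SD. At 0.5 SD it gives 4.9 to 6.7% on visit scores and 6.4 to 9.2% on change scores.

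**4. Direction.** The rates above are two-sided. Once the gate is nearly always passed, false findings in favour of LA occur in about 4.3 to 5.0% of trials, against a nominal 2.5%.

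**5. If the pairwise tests are adjusted.** Bonferroni over three pairs gives 0.05 / 3 = 0.0167 per test. Two independent visits then give 1 − (1 − 0.0167)² = 0.033; simulated rates are about 3.5% or less.

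**6. With one named visit.** The false LA versus SLA rate is 4.8 to 5.2% when the gate is nearly always passed.

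**7. Split results, as an illustration.** Assume an LA benefit over sham of 0.5 SD at t1 fading to 0.25 SD at t2, control worse by 0.5 SD and correlation 0.5. With 28 per arm, exactly one visit is significant in about 35% of trials and both in about 10%. With 40 per arm these are 46% and 16%.

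**The case against.** The strongest reply is that the plan has one primary test, the interaction at 5%, which matches the sizing and reproduces. If no arm differs, that test does protect the comparisons behind it, and false LA versus SLA findings stay at about 3% or less. A reader might infer that leaving two visits open nearly doubles the false-positive rate in general. The documents do not support that: it takes LA equal to sham, both clearly ahead of control, and unadjusted pairwise tests.

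A reader might also infer that each visit is to be tested at 0.05, or that a difference at either visit counts as primary success. Neither is written. The 0.05 rule is general, the adjustment is unstated rather than ruled out, and an analysis plan that is not shown may set one. Nor does the rate of false claims favouring LA exceed 5%; it roughly doubles from 2.5%.

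Finally, the split-result percentages rest on an assumed effect shape that the article does not give, and at 28 per arm they partly reflect low pairwise power.

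All of this stands, and it limits the size of the problem. It does not answer the main point. The interaction cannot show superiority over sham, and an adjustment over pairs would still not say which visit decides or how a split result is read. The time point is part of defining a primary outcome, so it belongs in the protocol.

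**Conclusion.** The point holds in a conditional form. The article fixes neither the visit nor the contrast that decides the primary PSQI comparison, and a result positive at only one visit has no stated meaning. That gap does not depend on any simulation.

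The inflation does depend on assumptions. With a shared device effect of 0.8 to 1.0 SD, LA equal to sham and unadjusted tests, the two-sided chance of a false LA versus SLA difference at t1 or t2 is about 8 to 10%, against about 5% with one named visit. At 0.5 SD it is about 5 to 9%, with no arm difference at most about 3%, and with Bonferroni over the three pairs about 3.5% or less. These figures assume equal variances, compound symmetry, within-patient correlation 0.3 to 0.7, no dropout and 28 to 40 per arm. The plan should be changed, but the point is no evidence that its error rate is inflated in every case.

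**What to change.** In the Primary outcome and Statistical methods sections:

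- Name one deciding visit, for example t1 at the end of the six-week treatment, and LA versus SLA as the primary contrast at two-sided 0.05, estimated from the same repeated-measures model.
- Test LA versus SLA at t2, and LA versus control, in a stated fixed sequence, each only if the preceding test is significant. This also settles how a split result is read.
- Do not test the arms against each other at t0.
- Report estimates with 95% confidence intervals at both visits, whatever the tests show.
- In the Sample size calculation section, state that the size was computed for the interaction and not for this contrast.

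The change needs no new patients or data, but it is more than wording, because the deciding test moves away from the one that was sized. It should be made, and the registry entry updated as the Trial status section provides, before any unblinding. The price is that a difference seen only at t2 can no longer be claimed as primary success.
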